## Abstract

**Background:**

The National Return of Unwanted Medicines (NatRUM) program in Australia is one of the few nationally coordinated, free-to-consumer schemes to dispose of unwanted medicines globally. This scheme has been in operation since 1996, however, little is known about public awareness of the scheme and its effectiveness in reducing unsafe disposal practices. The study objectives are to undertake a review of (1) the current use of the NatRUM scheme by consumers; and (11) to investigate disposal practices and beliefs of the general population.

**Methods/design:**

A two-stage, mixed-methods study will be undertaken. Stage One will include a nation-wide audit of a representative sample of unwanted medicine bins, collected by community pharmacies, for incineration. The audit will detail the type and amount of unwanted medicines collected and if they are subsidised on the national formulary (Pharmaceutical Benefits Scheme). Stage Two will include: (i) a large, representative, general population survey; and (ii) more detailed interviews with a sub-set of this sample, who take five or more medications. Results will quantitatively describe the awareness of the NatRUM scheme, disposal practices and the volume of unwanted medicines stored in the home. It will qualitatively describe beliefs and perceptions about storage and disposal practices.

**Discussion:**

It is anticipated that this study will provide valuable insights about how Australians dispose of unwanted medicines, their awareness of the NatRUM scheme and how the scheme might be strengthened. Results will inform the Federal Department of Health and NatRUM Ltd. Board at a local level, as well as other countries who are yet to develop or implement coordinated disposal schemes. A number of challenges are expected, including ensuring the consistency of medicines terminology during the bin audit and recruiting a representative sample of Australians for the general population survey. Results of this study will be widely disseminated to support the translation of findings into practice.

## Background

Global medicine use with both prescription and over-the-counter (OTC) medicines is increasing, and estimated to reach 4.5 trillion doses in 2020; an increase of 24% from 2015 [1]. The implications of this increase are that in 2020 more than half of the world’s population will take more than one dose of medicine per day, and this change will be driven largely by increased use in emerging markets such as India, China, Brazil and Indonesia [1]. Echoing this worldwide trend, at a local level in Australia, prescription volumes have increased 15% over the last five years (2010–2015) to 211.4 million in the year ending June 2015 [2]. Minimising medicines waste and instituting appropriate disposal practices for unwanted medicines (that is, expired medicines, and in-date medicines that are no longer required, including used or unused packs), are consequently a global issue.

Adverse consequences of inappropriate disposal of medicines in landfill and via the sewerage system have been reported, including identity theft from personal information on medicine labels disposed in garbage [3], and concentrations of medicines detectable in surface and drinking water [4, 5]. Similarly, adverse consequences from accumulation of unwanted medicines stored in the home present safety hazards such as accidental ingestion and security issues such as theft [6]. All of these issues pose significant environmental, economic and public health concerns.

Routes for medicines to enter the environment include excretion from the human body (metabolites and parent compound) through urination/defecation, washing off directly from the skin whilst bathing (e.g. creams and ointments), or from inappropriate disposal in the toilet, sink and/or household garbage [3, 7, 8]. Sewerage systems are not equipped to remove medicines and their metabolites effectively and hence these may be discharged into waterways and subsequently into drinking water supplies [9]. Medicines disposed in the garbage end up in landfill and may leach out more slowly into water systems [10]. Once in waterways, medicines and their metabolites may affect plant, marine and animal life, and potentially human life [11, 12]. Future research will determine the degree to which concentrations may be harmful to human health.

As the volume of medicines wastage in communities increases, the environmental and public health effects, and risks outlined here, will be compounded with significant financial implications [13]. Limited health service budgets need cost-effective medicine use. Reducing the volume of unused medicines in the home is a complex issue as highlighted by the 2009 evaluation of NHS medicines wastage in the United Kingdom [14]. The evaluators in their recommendations emphasised the need to focus on improving health outcomes rather than reducing waste alone; opportunities included reducing excessive and irrational prescribing with regular reviews of medication regimens by doctors and pharmacists (e.g. Medicines Use Review programs), targeting adherence support for those starting new medicines, or finishing courses of medicines and reviewing repeat prescribing and dispensing processes [14, 15]. Any changes need to be considered alongside consumer convenience and administrative burden.

Research studies on household disposal practices for unwanted medicines around the world have identified that the most popular methods were pouring them down the toilet or sink, or throwing them in the garbage [3, 16]. A systematic review of global disposal practices found that the method preferred was influenced by the formulation and/or type of medicine: sinks or toilets were favoured for liquids, whilst solid and semi-solid forms such as tablets/capsules and ointments/creams, were disposed of in household garbage. Medicines considered to be more harmful, such as antibiotics, were more often returned to a pharmacy, whereas OTC ‘everyday’ products such as cough medicines were poured down sinks or toilets [16].

The aforementioned systematic review also identified that ‘confusion exists about the proper way of medication disposal’ (pg. 297) in many countries because standardised guidance and protocols on appropriate disposal of unwanted medicines, including access to a nationwide disposal system, were lacking [16]. In contrast, in Sweden, where a national disposal system using pharmacies was established in 1971, 73% of households surveyed, reported that they would use this method for disposing of their unwanted medicines. Only 3% of those surveyed reported disposing of their unwanted medicines in the garbage and none had poured medicines down the drain [17].

In July 1998 the Australian Government also introduced a program that provides a safe, free, and convenient means for the public to return unwanted and out-of-date medicines to community pharmacies; the National Return and Disposal of Unwanted Medicines (NatRUM) scheme. The medicines collected in specific RUM (Return of Unwanted Medicines) bins are then disposed of by high-temperature incineration (which is the Environment Protection Authority (EPA) approved method of disposal) [18]. However, whilst national medicine collection and disposal schemes that are free for the public, such as the Swedish and Australian programs, are becoming more common (e.g. in the United Kingdom and European Union), these are not standard in all countries.

Incineration of medicine waste collected via the Australian NatRUM scheme has increased considerably over time; in the 2015/2016 financial year 705,079 kg of medicine waste was incinerated, an increase of 7.7% compared with the previous year [18]. Two reviews of the NatRUM scheme were undertaken in 2005 and 2013 [19, 20]. The 2005 study interviewed a sample of 605 consumers returning unwanted medicines to community pharmacies in one state of Australia. Most of these consumers had used the NatRUM scheme previously after being informed about it by a pharmacist. The main reasons for consumers to return medicines were: because it had expired (31%), person taking medicine (usually a relative) was deceased (26%), or the medicine (prescription) had been changed (8.5%) [19]. The 2013 study was a medicine wastage audit of a random sample of 686 RUM bins collected from six regions of Australia. Most of the returned medicines were scheduled (e.g. prescription, pharmacist-only, or pharmacy-only medicines), and almost half were still within their expiry date [20]. Six of the 10 most commonly returned medicines were also the most frequently dispensed under the Pharmaceutical Benefits Scheme (PBS).^1^

Despite this increasingly used nation-wide scheme, information about household waste disposal practices from the Australia Bureau of Statistics in 2012 estimated that more than one million Australian households had discarded unwanted medicines, drugs or ointments with their usual garbage [21]. For households who had disposed of these items in the last 12 months, 55% had disposed of them with the usual household garbage and 14% had poured them down the drain or toilet [21].

The present study extends previous work, providing a timely opportunity to explore the current use of the NatRUM scheme and will offer further insight into practices and awareness from a sample of the general public and healthcare workers about this free national scheme, and their attitudes and behaviours towards the storage and disposal of unwanted medicines.

### Study design overview

This mixed-methods study will involve two stages. Stage One will undertake an Australia-wide audit of a representative sample of RUM bins. The objectives of this stage are:To quantitatively describe the amount and types of medicines returned to pharmacies using a statistically valid sample of returned RUM bins from all states and territories of Australia; andTo identify the proportion of waste that is PBS-subsidised and to extrapolate the value of ‘wastage’ to the PBS.

In Stage Two a two-step general population survey will be conducted. Step One will utilise an online household survey with a general population sample. Step Two will invite a sub-set of survey respondents from Step One who take five or more medicines, to participate in a telephone interview. The objectives of Stage Two are:To assess general population awareness of: the NatRUM scheme; practices for the disposal of unwanted medicines; and the risks of accumulating medicines;To identify general population practices for household disposal of unwanted medicines in the previous 12 months;To quantitatively describe the volume of unwanted or expired medicines stored in the households of a sub-set of the general population with higher medication burden; andTo qualitatively explore the storage and disposal practices of a sub-set of the general population with higher medication burden.

## Methods

### Stage one

The RUM bin audit methodology was adapted from the earlier audit conducted in 2013 [20]. This will allow a number of audit outcomes to be compared to the 2013 outcomes. Amendments will address limitations of the earlier audit, and changes to the NatRUM scheme as it has grown over the intervening period e.g. increased number of incineration sites from one to three.

#### Sample size and RUM bin selection

The design of the audit must ensure that a statistically relevant sample of RUM bins from all Australian states and territories are included (*n* = 8). Over the last three years (2013–2015), data provided by NatRUM Ltd. showed that an average of 10–12,000 bins per month were collected for incineration. For the purposes of calculating the minimum sample size for a statistically valid sample of RUM bins in this study, 12,000 bins per month was used in the Raosoft® sample size calculator (http://www.raosoft.com/samplesize.html); a minimum of 373 bins would need to be sampled (assuming 5% margin of error and 95% confidence interval).

Table 1 outlines the number of RUM bins calculated to ensure an Australian-wide representative sample of 373 bins. Based on the 2013 audit [20], it was estimated that an additional 10% (37 bins) would require inspection to ensure that no bins contained more than 50% as loose tablets/capsules i.e. without any form of packaging (see exclusion criteria listed in *Bin contents and inspection* section).

**Table 1 Tab1:** Selection of RUM bins required for audit^a^

State/territory	Average number of pallet collections per month	Average number of bin collections per month	Percentage of bins (%)	Number of bins to be audited
Australian Capital Territory	2	96	0.8	3
New South Wales	79	3792	30.4	113
Northern Territory	2	96	0.8	3
Queensland	48	2304	18.5	69
South Australia	37	1776	14.2	53
Tasmania	4	192	1.5	6
Victoria	68	3264	26.2	97
Western Australia (including Christmas Island)	20	960	7.7	29
TOTAL	260	12,480	100	373

^a^
*Pellet Collections by region (first six months of 2015/2016): National data (excluding Western Australia) provided by NatRUM Limited. Data for Western Australia provided by the Western Australia Incineration Site*

Incineration contractors at the three licensed plants (located in Victoria, Queensland and Western Australia) will be requested to randomly select and set aside one bin in every ten from each sequential pallet arriving from all states or territories in the month prior to the audit, until the total (plus 10%) for that site is achieved.

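### Taking one bin in ten until a site total is reached ends selection after about a third of arriving pallets and does not secure bins from the smallest jurisdictions

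*Protocol article*

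**What the plan says.** All of this is in the protocol article. The Stage One objectives (Study design overview) call for a "statistically valid sample of returned RUM bins from all states and territories of Australia", and the section on sample size and bin selection repeats that the design has to include all eight.

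That section gives the sample size: "12,000 bins per month was used in the Raosoft® sample size calculator", and "a minimum of 373 bins would need to be sampled (assuming 5% margin of error and 95% confidence interval"). For bins that will be excluded, "it was estimated that an additional 10% (37 bins) would require inspection", so 373 + 37 = 410 are to be set aside. Table 1 splits the 373 by state or territory in proportion to volume. Its total row reads "TOTAL 260 12,480 100 373" (pallets, bins, per cent, bins to audit). One of the two smallest rows reads "Australian Capital Territory 2 96 0.8 3".

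During the month before the audit, contractors at the three plants are to "randomly select and set aside one bin in every ten from each sequential pallet arriving from all states or territories", and to continue "until the total (plus 10%) for that site is achieved". The article gives no totals by site. It does not say which states feed which plant, or that each Table 1 count must be met before a plant stops.

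**The concern.** Two parts of the instruction do not fit the target.

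The first is the fraction. One in ten is about three times the rate that the target needs, so the total is reached early in the month. Every pallet arriving after that has no chance of selection.

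The second is the unit on which selection stops. Coverage is required for eight jurisdictions and the counts are set for eight, but the stop is applied at three plants. A plant can reach its total on bins from the large states before a pallet from a small one arrives.

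At stake is the claim of a national sample covering every state and territory, from which the value of PBS wastage is to be extrapolated. Selection cannot be repaired afterwards, because bins that are not set aside are incinerated.

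**Working it through.** **Inputs from the sample size section and Table 1:** N = 12,000 bins a month; margin 5%; 95% confidence; 373 bins plus 37; 260 pallets and 12,480 bins a month; 2 pallets each for the ACT and the Northern Territory, 4 for Tasmania. **Assumed, not in the article:** a proportion of 50% in the sample size; random order of pallet arrival; the within-pallet correlation (ICC), shown as a range.

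**1. The plan's own figure.** With x = 1.96² × 0.25 = 0.9604,
n = N·x / [(N − 1)·0.05² + x] = 12,000 × 0.9604 / (11,999 × 0.0025 + 0.9604) = 372.3, rounded up to 373. The figure reproduces, as a single bin-level proportion under simple random sampling.

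**2. Fraction against target.**
- Bins per pallet: 12,480 / 260 = 48.
- One in ten: 4.8 per pallet, or 1,248 over a full month.
- Wanted: 410, which is one in 12,480 / 410 = 30.4.
- Pallets needed: 410 / 4.8 = 85.4, which is 33% of 260. At 5 bins per pallet it is 82 (32%); at 4 it is 103 (39%).
- Western Australia alone gives the same share: 29 × 1.1 = 31.9 bins, and 31.9 / 4.8 = 6.6 of 20 pallets, or 33%.

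**3. Coverage if only the site total binds.** Treat the first 85 of 260 pallets as a random draw. A jurisdiction with k pallets is missed with probability C(260 − k, 85) / C(260, 85).
- ACT (k = 2): (175 × 174) / (260 × 259) = 0.45. The Northern Territory is the same.
- Tasmania (k = 4): (175 × 174 × 173 × 172) / (260 × 259 × 258 × 257) = 0.20.
- ACT or Northern Territory missed: 2 × 0.452 − 0.203 = 0.70.
- At 103 pallets: 0.36, 0.36 and 0.13.

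This pools the three plants, because the article gives no state-to-plant mapping. Leaving out Western Australia (79 of 240 pallets) still gives 0.45 for the ACT.

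**4. Coverage if the state counts bind.** The ACT and the Northern Territory each need 3 bins, or 3.3 with the reserve. One pallet supplies 4 or 5, so neither is missed. Each state still fills its count from about a third of its pallets (33% to 34% in every row of Table 1).

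**5. The 5% margin.** Margin = 1.96 × √(0.25 × DEFF / 373) × √[(12,000 − 373) / 11,999], with DEFF = 1 + (4.8 − 1) × ICC.

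| Assumed ICC | DEFF | Margin |
|---|---|---|
| 0 | 1.00 | 5.0% |
| 0.01 | 1.04 | 5.1% |
| 0.05 | 1.19 | 5.4% |
| 0.10 | 1.38 | 5.9% |

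**The case against.** The best defence is that the Table 1 counts are meant to bind. The article gives no site totals, so they can only be built from the state rows, and those rows were calculated to give a national sample. A contractor might well fill them row by row, and step 4 shows that coverage would then hold. The training tools and protocols are available on request and may say so. State of origin is recorded for each bin, so a shortfall would be seen.

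Much of this stands: the probabilities in step 3 belong to one reading only. But a site total is a sum of rows, and meeting the sum does not mean that each row is met. Recording origin would reveal a gap without filling it. The early stop remains on either reading.

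It is also fair to say that harm from the early stop is not shown. Table 1 gives monthly averages, so a third of arrivals is a third of the month only if flow is even, and nothing suggests that early and late bins differ in content.

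A reader might infer two stronger points. One is that the audit fails its 5% margin. The documents do not support this: the 373 reproduces, and any loss depends on an ICC that they do not give and is under one percentage point up to 0.10. The other is that 3 or 6 bins are too few for state estimates. The objectives are national, and no separate estimate for a small jurisdiction is promised.

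**Conclusion.** The concern holds as a mismatch between the selection rule and its target. From the protocol's own figures, one bin in ten yields about three times the number wanted, so selection ends after about 85 of 260 pallets (82 to 103, depending on rounding). This needs no assumption beyond average flow.

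The stop by site does not secure the required coverage of all eight jurisdictions. The size of that risk, about 0.45, 0.45 and 0.20 for the ACT, the Northern Territory and Tasmania, assumes random arrival order and that only the site total binds. It falls away if the state counts bind, and the article has to say which applies.

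This is a problem of coverage, and only slightly one of precision. The 5% is a national figure for a bin-level proportion under simple random sampling. Taking several bins from each of the first pallets is not simple random sampling, and the figure does not carry over to the PBS dollar value.

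**What to change.** **Stop by state.** Use the Table 1 count plus 10%, rounded up: ACT 4, Northern Territory 4, Tasmania 7, Western Australia 32, South Australia 59, Queensland 76, Victoria 107, New South Wales 125. These sum to 414, against 410 now; the 4 extra come from rounding.

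**Spread selection over the month.** Set aside about two random bins from every 48-bin pallet (1 in 24), then draw each state's count at random from those. This gives 260 × 2 = 520 bins at average flow, and 10,000 / 24 = 417 at the low end of the volumes that the article reports. Simply changing the fraction to one in 30 would not be enough: 10,000 / 30 = 333, below 373 before any exclusion.

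**Allow slack in the small jurisdictions.** Two bins from each of two pallets gives the ACT and the Northern Territory exactly 4, with nothing spare if a pallet fails to arrive. Taking four per pallet there and in Tasmania adds 2 × (2 + 2 + 4) = 16 bins at average flow.

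**Restate precision in one sentence.** Say that the 373 and the 5% refer to a national bin-level proportion under simple random sampling, that the margin widens slightly if bins on a pallet are alike, and that it does not apply to the PBS value.

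The cost is a revised instruction to three contractors and storage of roughly 110 to 125 more bins at average flow (520 or 536 against 410), kept for the whole month. The number audited is essentially unchanged.

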#### Data collection and training

Data collection tools and protocols developed specifically for the 2013 NatRUM audit were reviewed and refined to ensure that the audit will build on, and extend, the evidence base; e.g. whether medicines have been used (opened or full pack) and calculating the proportion of medicine that is returned (compared with 2013 where all medicine packs were treated as unopened and 100% contents were assumed) [20]. Additional variables were identified from a similar audit in New Zealand (DUMP project [22]) and in consultation with the NatRUM Ltd. Board. Table 2 outlines the variables, to be included in the audit. A purpose-built database has been developed in Microsoft Access®. We used Australian Medicines Terminology (AMT) - a subset of the SNOMED CT-AU clinical terminology, supported by the Australian Digital Health Agency (http://www.digitalhealth.gov.au/get-started-with-digital-health/what-is-digital-health/clinical-terminology remove extra line here and rejoin sentence). This national terminology unambiguously identifies branded and generic medicines commonly used in Australia. It includes a list of most prescription and OTC medicines and complementary products sold in Australian pharmacies, allowing generic and/or trade names to be easily searched and data such as form, strength and original quantity to be easily selected. For items not available in this list, manual entry of the name of the product, form, strength and original pack quantity will be required. The database and data collection process have been piloted with three RUM bins at the Queensland incineration plant and a number of modifications were implemented. The Access® database has been loaded onto laptop computers for data entry in real time at each incineration site.

**Table 2 Tab2:** Variables to be included in RUM audit and post-audit analyses

Characteristics of RUM bins	Source of container (state or territory)
	Container weight
	Percentage filled
Content of RUM bins	Medicine characteristics
	Brand name
	Generic name
	Manufacturer
	Medicine schedule (i.e. unscheduled, S2, S3, S4 or S8)
	Therapeutic category (PBS code)
	Medicine dose
	Form of medicine
	Whether medicine is PBS subsidised or private
	Whether medicine is expired
	Packaging of medicine included
	Evidence of attempted destruction for S8 medicines
	Presence of inappropriate items (e.g. sharps, rubbish)
	Complementary and alternative medicines
	Medicine in a sample package
	Medicines characteristics once dispensed
	Year dispensed^a^
	Quantity dispensed^a^
	Quantity returned^a^
	Evidence of medicine use^a^
	Proportion of dispensed quantity unused^a, b^
	Medicine unlabelled
	Category of medicine dispensing (e.g. concession or general)^a^
	Dose administration aids (DAA)
	Type of DAA
	Proportion of medicines unused in DAA

*PBS = Pharmaceutical Benefits Scheme; S2 = Pharmacy medicine; S3 = Pharmacist-only-medicine; S4 = Prescription medicine; S8 = Controlled medicine*

^a^
*These variables extend the evidence base of data collected during the 2013 audit*

^b^
*Only medicines packaged as foil strips/blisters will be counted and assumptions used in the New Zealand DUMP project audit* [22] *will be applied to documentation of quantity of returned inhalers, creams, liquids*

Audit training tools, including a data collection protocol and quality assurance procedure, and Occupational Health and Safety (OH&S) Standard Operating Procedure (SOP) were developed in consultation with incineration plant managers, personnel from Griffith University OH&S and NatRUM Ltd. (all training tools and protocols are available from correspondence author on request).

Data collection will be conducted at each of the three incineration sites by research assistants, working in pairs (one person inspects and counts whilst the second enters the information into the database), under the supervision of the project Data Collector Manager, (a registered pharmacist). An additional research assistant will be available at each site to act in a quality control role and to provide cover for breaks and/or absences such as unexpected illness. Data collectors will be trained at each site to safely audit a RUM bin and to enter data into the Access® database. Training will include familiarisation with the specific auditing equipment including protective clothing (gloves, safety glasses, dust masks, coveralls), and tools (tongs, tweezers, scales), and a demonstration of how to safely open and assess the contents of a RUM bin. Training will also emphasise the importance of the confidential nature of bin contents including any pharmacy, prescriber and patient information. A representative from Griffith University OH&S will be present for this training.

